## 7. *Supplement distribution and community cooperation*

Supplementation will begin once the midwife has confirmed the pregnancy and administered the enrollment questionnaire. The supplements are to be taken daily and will be distributed in packages containing 30 tablets, as is the current MOH practice with the iron/folate tablets. The pregnant women are instructed to come back each month to obtain their next batch of tablets. Based on the current rate of antenatal clinic attendance, we anticipate that a pregnant woman will see the midwife approximately six times and will obtain supplements. If a trial participant is late for an antenatal visit, the midwife's assistants will visit the woman at home to remind her, and provide the supplements. Supplement distribution will continue until 12 weeks postpartum or 12 weeks following a miscarriage or stillbirth. In order to maximize enrollment and to ensure widespread distribution of supplements and proper recording, midwives and their assistants will receive incentives for their work on the project. In addition, targeted social marketing and educational activities will be carried out to promote use of the supplements.

## 8. *Data collection*

In addition to the distribution of supplements, midwives will perform and record the results of routine physical examinations, attend deliveries, and detect maternal and neonatal deaths. These procedures and data are already included as part of the normal MOH prenatal visit protocol. In addition, HKI data collectors will collect data at enrollment and 36 weeks during each pregnancy and at 12 weeks postpartum. The data collected on each of the sample groups is summarized below.

| Sample Group                     | Data to be collected            | Timing of data collection                                                                            | Data Collector                 |
|----------------------------------|---------------------------------|------------------------------------------------------------------------------------------------------|--------------------------------|
| Total sample
(126,000)        | Demographic baseline survey     | Prior to supplementation trial                                                                       | HKI data collectors            |
|                                  | Enrollment & informed consent   | First visit to midwife                                                                               | Midwife                        |
|                                  | Socio-economic & nutrition data | Within one week of enrollment & at 36 weeks of gestation                                             | HKI data collectors            |
|                                  | ANC Exam reports                | ANC visits and delivery                                                                              | Midwife                        |
|                                  | Birth assessment                | Delivery or within 48 hours                                                                          | Midwife or HKI data collectors |
|                                  | Maternal Child health visit     | Seven days after delivery                                                                            | Midwife                        |
|                                  | Maternal Child health visit     | 12 weeks postpartum                                                                                  | HKI data collectors            |

## 9. *Biochemical determinations*

At enrollment, all women will have a finger prick blood spot taken for the purpose of determining anemia using the UNICEF anemia color chart kit. This is currently utilized by many midwives and is part of the normal government pre-natal consultation protocol. A smaller number of randomly selected women will be enrolled into a sub sample of 20,000 women in which 2-3 ml venous blood will be drawn at baseline and at one other time point during pregnancy or post-delivery, resulting in 1-1.5 ml plasma from each blood draw. The time points for the second blood draw are 1 month post enrollment, 36 weeks of gestation, 1 week post delivery, and 12 weeks post delivery. This will result in 4 groups of 5000 plasma samples each. Cost, logistics, and limited plasma volume precludes the analysis of all micronutrients in each plasma specimen, nor is this statistically necessary to determine meaningful changes in micronutrient status. Therefore, each group of 5000 blood samples will be randomly sub-divided into 5 groups of 1000 samples each, with individual groups being analyzed for one of 5 specific combinations of nutrients comprised of minerals, B vitamins, carotenoids and vitamins A and E, antioxidants, and specific inter-related nutrients. This general approach will optimize meaningful assessment of micronutrient indicators, and their association with the measured clinical outcomes, at multiple crucial times throughout pregnancy and postpartum. This approach will allow detection of a 30% or less change (power=80%,  $p<0.05$ ) in prevalence rates of at least 10% of individuals with low nutrient status.

Because malaria exists in many villages and is a risk factor for maternal anemia and pregnancy complications, a blood slide will also be prepared at each time point for the

subsample. This will also allow estimation of the effects of micronutrient supplementation on maternal malaria. Data on micronutrient status will also allow determination of associations between specific micronutrients and child health outcomes such as low birth weight and neonatal mortality. Blood samples will be processed in Mataram, and shipped to Jakarta for laboratory analysis.

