## **SUMMIT activity design and methodology**

*Outcomes:* The SUMMIT activity is a controlled trial designed to assess the relative impact of a prenatal multi-micronutrient tablet in comparison to the current MOH iron/folate tablet on frequency of maternal mortality as assessed by both the maternal mortality ratio (MMR), defined as maternal deaths per 100,000 live births, and the maternal mortality rate (MMRT), defined as the death of a woman while pregnant or within 42 days of termination of pregnancy from any cause aggravated or related to the pregnancy, expressed per 100,000 pregnancies. Two additional main outcomes of the SUMMIT activity are proportion of low birth weight infants, and infant mortality, including neonatal mortality. Secondary outcomes to be assessed include maternal morbidity, neonatal development, and nutritional status during pregnancy and lactation. In addition to examining the effect of multi-nutrients, we will document the effect of education and social marketing of the SUMMIT activity by comparing outcome rates in the iron/folate arm of the intervention area to corresponding rates in designated villages where standard prenatal care practice will continue. In a 20% subsample of pregnancies biochemical status for micronutrients, including, iron, zinc, and vitamin A, will be determined.

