## 3. *Sample Size*

The sample size is influenced by the minimal desirable detectable effect of the intervention, the event rate of the outcome, and the duration of the intervention. The desired detectable effect is influenced by the magnitude of the plausible effect size and the importance of the preventable event. Initial estimates of a plausible effect size of multi-micronutrient supplementation on maternal mortality can be guided by childhood

mortality-related effects observed for other micronutrients such as vitamin A and iodine, which range from 20-70%. While acknowledging that physiological differences between children and pregnant women limit the utility of such information, additional perspective is gained from the results of the NNIPS-2 study which described a vitamin A-mediated 40% reduction in mortality related to pregnancy. Given the relatively low-cost of a prenatal nutrient-based intervention, the documentation of a 20-30% effect, especially under programmatic settings, would be important. The estimates of the maternal mortality ratio in various districts on Lombok range from 400 to 800 maternal deaths per 100,000 live births. For this intervention the unit of randomization will not be the individual woman, but the area or cluster of communities administered by the midwife. This improves logistical feasibility but reduces statistical power due to the potentially correlated outcomes within each cluster. Given the estimated between-cluster variability in MMR, we have calculated that a 20% increase in sample size is needed to compensate for the loss of statistical power from the cluster-based randomization. We further anticipate a loss to follow-up of approximately 10%. Lastly, because not all pregnancies result in a live birth, it is estimated that the required sample size be increased an additional 15% to compensate for abortions, miscarriage, and stillbirths. Given these factors, the sample size table below presents the number of pregnancies required to obtain significance for various observed reductions in MMR for the proposed 2-arm design.

| Detectable
reduction
(%) | Total pregnancies needed by baseline MMR
(deaths/100,000 live births) |                |                |
|-----------------------------------------|----------------------------------------------------------------------------------|----------------|----------------|

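### The 80% power stated for the biochemical subsample names no comparison; for the two supplements at one time point and 10% prevalence it is about 40%

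*Protocol*

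**What the plan says.** Section VIII.B.9 (Biochemical determinations) describes a subsample whose members are "enrolled into a sub sample of 20,000 women in which 2-3 ml venous blood will be drawn at baseline" and once more later. The second draw falls at one of four times: "This will result in 4 groups of 5000 plasma samples each". Then "each group of 5000 blood samples will be randomly sub-divided into 5 groups of 1000 samples each". Any one of these smaller groups is assayed for a single nutrient panel out of five. The section presents this layout as suited to assessing nutrient status at several points in pregnancy and after delivery. It closes with the claim "This approach will allow detection of a 30% or less change", at 80% power and p<0.05, for prevalences of low status of 10% or higher. It gives no comparison, number per arm, sidedness, or allowance for clustering or loss.

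Section VI.B (Specific objectives) lists maternal micronutrient status among the outcomes on which the two supplements are to be compared. The sample size section describes its table as "for the proposed 2-arm design".

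The size of the subsample is given in two ways. The Executive Summary has "In a 20% subsample of pregnancies biochemical status for micronutrients"; section VIII.B.9 has "enrolled into a sub sample of 20,000 women", and the data collection table agrees with the latter.

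**The concern.** The group of 1,000 is what remains after splitting by time of second draw and by panel, but before splitting by arm. If the 80% is read as power to compare supplements at a given time, which is the natural reading next to the stated objective, the number per arm is about 500. That is well short of what 10% against 7% needs.

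Micronutrient status is the link between the tablet and any effect on mortality or birth weight. A non-significant arm difference at a single time point, for a deficiency of low prevalence, could be taken as evidence that the supplement did not change status, when the study had limited power to show the change it names.

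**Working it through.** **Inputs**
- Subsample 20,000; four second-draw times; five panels per time (section VIII.B.9).
- Two arms (section VIII.B.3). Equal allocation is inferred from 63,000 of 126,000 pregnancies being in the iron/folate arm.
- 80% power, p<0.05, prevalence at least 10%, change of 30% (section VIII.B.9). The hardest case is 10% against 7%. Sidedness is not stated; two-sided is taken.
- Design effect 1.2: the 20% inflation that section VIII.B.3 gives for maternal mortality. Its use here is an assumption, shown as a sensitivity check.

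**Cell size**

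20,000 / 4 = 5,000 per time; 5,000 / 5 = 1,000 per panel and time; 1,000 / 2 = 500 per arm. With design effect 1.2, 500 / 1.2 ≈ 417 effective.

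**Arm comparison at one panel and one time point**

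Pooled-variance normal approximation:

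power = Φ{ [ (p1 − p2)√n − 1.96·√(2p̄(1−p̄)) ] / √(p1(1−p1) + p2(1−p2)) }

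With p1 = 0.10, p2 = 0.07 and p̄ = 0.085:
- √(2 × 0.085 × 0.915) = 0.3944
- √(0.0900 + 0.0651) = 0.3938
- n = 500: (0.03 × 22.361 − 1.96 × 0.3944) / 0.3938 = −0.259, so power = **39.8%**
- n = 417: power = **34.2%**

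A simulation of the same test at 500 per arm gave 39.7%. A one-sided test gives 52.2%.

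Number needed per arm for 80%: [(1.96 × 0.3944 + 0.8416 × 0.3938) / 0.03]² ≈ 1,355.4, rounded up to 1,356, against about 500 available.

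**Power for a 30% reduction, by prevalence, 500 per arm**

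| Prevalence | Power |
|---|---|
| 10% | 40% |
| 15% | 57% |
| 20% | 71% |
| 24% | 81% |

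The 80% line is crossed at about 24% prevalence, or about 27% with design effect 1.2. At 10% prevalence the reduction detectable with 80% power is about 47%, or 51% with design effect 1.2.

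**Comparisons that do reach the stated 80%**

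1. *Arms, pooled over the four second-draw times.* Each woman has one second sample, so a panel has 4 × 500 = 2,000 women per arm. For 10% against 7%: (0.03 × 44.721 − 0.7730) / 0.3938 = 1.444, so power = **92.6%** (**87.4%** with design effect 1.2, 1,667 effective).
2. *Within-woman change from baseline (McNemar).* The share low at both draws is p11 = p1p2 + ρ√(p1(1−p1)p2(1−p2)), and the discordant share is pd = p1 + p2 − 2p11. Then power = Φ{ [ (p1 − p2)√n − 1.96√pd ] / √(pd − (p1 − p2)²) }.
   - 1,000 pairs (both arms together): 80% needs ρ of about **0.27**. There p11 = 0.0277, pd = 0.1147 and power = 80.1%.
   - 500 pairs (one arm): 80% needs ρ of about **0.64**.

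   The documents give no correlation, so these values are assumptions.

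**Subsample size**

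20% of 126,000 = 25,200; 20,000 / 126,000 = 15.9%.

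**The case against.** The strongest reply is that section VIII.B.9 never ties the 80% to an arm comparison at one time point. Every woman is bled twice, the section speaks of change in status, and section VIII.B.13 says samples are analysed only once pairs exist. Read as a before-and-after change in the 1,000 women of a group, the claim holds at a modest correlation of about 0.27. This stands to the extent that a reader might infer that the 80% is simply false, or that pooling is the only way to save it. The documents support neither inference, because the comparison is left open.

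The reply does not remove the problem. A before-and-after change over both arms together mixes the two supplements with the course of pregnancy, so it does not estimate the difference between supplements that section VI.B asks for. Within one arm the correlation needed rises to about 0.64, and that test is still not an arm contrast.

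Two further points on that side are fair. The shortfall is confined to prevalences between 10% and about 24%. The one zinc-deficiency figure in the protocol, for postpartum women in Indonesia, is 24% (section III.D), where the claim just holds before clustering. Nutritional status is also a secondary outcome in the Executive Summary, so no primary conclusion depends on it.

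**Conclusion.** The stated power is not tied to a comparison, and it is not delivered for the one that the objectives call for when that comparison is made at a single time point. At 10% prevalence, power is about 40% (34% with design effect 1.2) against 80% stated, rising to 80% at a prevalence of about 24% (27%). This rests on equal arms, a two-sided 5% test and no loss of second samples; any loss would lower power further.

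It would go too far to say that null results in general had less than an even chance of being positive. That holds only near the 10% floor; at 15% prevalence, power is already 57% before any clustering allowance. Severity is moderate: a stated power figure needs correcting, on a secondary objective. The mismatch between 20% and 20,000 is minor and does not enter the power calculation.

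**What to change.** In section VIII.B.9:
- Name the comparison, the number per arm (about 500 per panel and time point) and the design effect assumed.
- Restate the per-time-point claim between arms: 80% power for about a 47% reduction at 10% prevalence (51% with design effect 1.2), or for a 30% reduction at a prevalence of about 24% or more (27%).
- Quote 30% at 10% prevalence only for the arm contrast pooled over the four second-draw times, stratified by time and adjusted for the baseline value of the same nutrient (about 2,000 per arm; 93%, or 87% with design effect 1.2, before any gain from adjustment).
- Give one subsample size, either 20,000 or a percentage that matches it, in the Executive Summary and section VIII.B.9.

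The cost is wording and an analysis choice; no more blood is drawn. The trade-off is that a pooled effect averages one month after enrolment with 12 weeks after delivery and gives up the time-specific picture. The per-time-point estimates should therefore still be reported, with their more limited power stated.

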## *10. Verbal autopsies*

The community will be encouraged to inform the midwife as soon as possible of any complications of pregnancy or delivery, including death. Pregnancies will be tracked until a final visit at 12 weeks postpartum. Additional deaths will be detected through the ongoing demographic surveillance system. This will allow the trial to include all maternal and infant deaths beyond the first 12 weeks. Through use of the existing MOH/WHO guidelines, a verbal autopsy tool will be developed, with which the midwives will determine [1] that a death which occurred was a maternal death and if possible, [2] the cause of the death. The same tool will be used by two medical doctors to independently verify the cause of death. In case of discrepancy between the results of the verbal autopsies performed by the two physicians, data will be jointly re-assessed to reach consensus. The focus of the verbal autopsy will be to ensure that a death that occurred was due to a pregnancy-related cause and occurred during pregnancy or up to 6 weeks after delivery or termination of pregnancy. This will be a crucial part of evaluating the impact of SUMMIT on MMR and MMRT.

## *11. Supervision, compliance and quality control*

To assure high quality data collection and recording, a variety of checks and monitoring visits will be conducted. Midwives will initially receive an update training and be familiarized with specific additional aspects of data collection for the trial. The HKI maternal morbidity workers will also provide additional guidance regarding proper data reporting methodology. Assessment of compliance will be very important in this intervention and this will be monitored by midwives at each antenatal visit by pill counting. Additional HKI supplementation monitors will carry out spot-checking of pill counts on a 20% subsample each month, so that each woman in the trial will be visited at least once during the average supplementation period of 6 months. In some cases a sample pill will be obtained to allow post-trial verification of allocation/distribution procedures. Assessment of social perceptions and attitudes toward pre-natal supplements, including side-effects, will also be determined by qualitative assessment methodologies. These data will be cross-referenced to the biochemical micronutrient indices determined in the subsample of women. This combination of activities will allow two compliance indices to be determined for each woman enrolled in the trial. One index will be comprised of the actual compliance data, and the other will be an estimated consumption index based on perceptions and other factors found to be predictive of use of prenatal supplements and change in micronutrient status.

## *12. Data management and analysis*

The first check of the forms will be performed in the field by the field supervisors. Data entry will be done using the *SPSS for Windows* program. Data will be entered in batches, and 10% of each batch will be cross-checked by data-entry supervisors. Batches for which unacceptable error rates are obtained will be re-entered and checked until acceptable

quality standards are met. The data-entry program will prohibit entry of invalid or impossible values and generate a query for follow-up. After data have been entered, additional outliers will be identified and checked against the original questionnaires. Queries regarding unclear or incomplete data will be referred to the field for appropriate follow-up. This system has been field-tested by the HKI NSS and functions well. Primary analyses will compare key outcome event rates event rates, MMR, MMRT, PNMR, and LBW in the multi-micronutrient group with the iron/folate group. However, the SUMMIT activity will not only provide information concerning the impact of micronutrients on these indicators, but it will also assess the specific impact of activities accompanying the intervention such as promotion of prenatal care and social marketing. This will be done by comparison of event rates in the pre and post-intervention areas for the iron/folate arm. This enables one to individually assess the impact of the various components of the SUMMIT activity on the key health outcomes. Relative cost-benefit analyses can therefore be carried out for the various interventions.

### *13. Consent procedures and ethical approval*

Before enrollment, all pregnant women will be informed about the project and that participation is voluntary. They will be informed that the trial will provide either the usual prenatal nutrients or the usual nutrients plus extra micronutrients. They will be asked to confirm, orally, that they understand the information given. Women who decline to participate in the trial will be provided with labeled GOI iron/folate tablets. The women that will be enrolled in the biochemical subsample will also be informed why blood samples are needed. They will be asked to consent to the blood drawing and if they understand the purpose of the blood collection. Because blood samples will be analyzed in batches and only after pairs are obtained, it is not anticipated that rapid feedback of biochemical information to the field site will be possible. Nevertheless, biochemical data indicative of a severely poor nutritional health will be sent to the field so that specific counseling or treatment can be administered.

Ethical approval for the SUMMIT activity has been obtained from the Joint Committee on Clinical Investigation of Johns Hopkins University School of Medicine, Baltimore, USA. (see Appendix 6). Approval of the protocol will also be required from the Medical Ethical Committee of the Indonesian Ministry of Health, and the intervention will only begin after such approval is granted.

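### Assaying subsample blood only once a pair exists leaves enrolment nutrient status unmeasured for women in the 36-week group who deliver before 36 weeks

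*Protocol*

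**What the plan says.** Protocol section VIII.B.9 (Biochemical determinations) describes a random subsample of 20,000 women with venous blood drawn "at baseline and at one other time point during pregnancy or post-delivery". The times for the "second blood draw are 1 month post enrollment, 36 weeks of gestation, 1 week post delivery, and 12 weeks post delivery". The expected yield is given without any allowance for missed draws: "This will result in 4 groups of 5000 plasma samples each", each group then being "randomly sub-divided into 5 groups of 1000 samples each", one per nutrient panel. The same section plans to relate the results to clinical outcomes, including "associations between specific micronutrients and child health outcomes such as low birth weight and neonatal mortality".

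The assay condition is not in that section. It is in VIII.B.13 (Consent procedures and ethical approval), where the reason given for not expecting quick feedback to the field is that "blood samples will be analyzed in batches and only after pairs are obtained". Neither section says what happens to an enrolment sample whose partner is never collected, and no substitute draw is given for a woman who delivers before her 36-week draw.

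**The concern.** Nutrient status at enrolment is fixed before the birth and needs no second sample to be useful. If its assay waits on a later draw, whether it is measured depends on what happens in between, and in one group that includes the timing of the birth itself. A woman assigned to the 36-week draw who delivers at 34 weeks has no pair. Her infant is among those most likely to be low birth weight or to die, so leaving her out selects on something closely tied to the outcomes being studied.

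The protocol makes this pathway plausible: sections II.A and III.B link anaemia and iron deficiency with preterm delivery. If poor status acts partly through early delivery, an association estimated only in women still pregnant at 36 weeks misses that part. An analysis plan cannot repair this, because a sample that was never assayed gives no value to analyse.

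**Working it through.** **Inputs from the protocol.** Subsample 20,000; four second-draw times; five panels (VIII.B.9). Low birth weight (LBW) 15 per 100 live births and neonatal mortality 46 per 1,000 (VIII.B.3, second table). Loss to follow-up about 10%, a 15% allowance for pregnancies without a live birth, and a maternal mortality ratio of 400-800 per 100,000 live births (VIII.B.3).

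**Inputs assumed, because the protocol gives none.** Births before 36 weeks: 3-8% of live births. Share of these that are LBW: 60-80%. Neonatal mortality among them: 10-20%.

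**1. The plan's own yield.** 20,000 / 4 = 5,000 per time point and 5,000 / 5 = 1,000 per panel. Both reproduce exactly, but only if no second draw is missed. With the protocol's 10% loss they become 5,000 × 0.9 = 4,500 and 1,000 × 0.9 = 900.

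**2. LBW cases without an enrolment value, 36-week group.** Share lost = (proportion born before 36 weeks × proportion of those LBW) / 0.15.
- Low end: 0.03 × 0.60 / 0.15 = 0.018 / 0.15 = 12%.
- High end: 0.08 × 0.80 / 0.15 = 0.064 / 0.15 = 43%.

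LBW among the women who can still be paired falls from 15% to (0.15 − 0.018) / 0.97 = 13.6% at the low end and (0.15 − 0.064) / 0.92 = 9.3% at the high end.

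**3. Spread over the whole subsample.** Only one group in four is affected in this way: 12% / 4 = 3% and 43% / 4 = about 11%.

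**4. Neonatal deaths, same method.** 0.03 × 0.10 / 0.046 = 6.5% and 0.08 × 0.20 / 0.046 = 35% of that group's neonatal deaths, or about 1.6-8.7% across the subsample.

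**5. What the selection can do to an association (illustration).** Assume 20% of women have low status, low status multiplies the risk of early delivery by 1.5 and does nothing else, and 70% of early births are LBW.
- With 5% early births overall, the early-birth risk is 0.05 / (0.8 + 0.2 × 1.5) = 4.55% with adequate status and 6.82% with low status. LBW among later births is (0.15 − 0.05 × 0.7) / 0.95 = 12.1% in both.
- Total LBW risk is 0.0682 × 0.7 + 0.9318 × 0.121 = 16.1% with low status and 0.0455 × 0.7 + 0.9545 × 0.121 = 14.7% with adequate status, a risk ratio of 1.09.
- Among women still pregnant at 36 weeks the ratio is 12.1 / 12.1 = 1.00.
- The same steps with 10% early births, outside the range used above, give 1.19 against 1.00.

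**6. Maternal death.** 20,000 × 0.85 × 0.004 = 68 and 20,000 × 0.85 × 0.008 = 136 deaths, or 0.3-0.7% of the women. Not all of these fall before the assigned draw.

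**The case against.** **The sentence concerns timing.** It sits in the consent section and explains slow feedback; the section that governs the assays never says that unpaired plasma is discarded. This is fair: permanent exclusion is an inference. But the wording states a condition for assay and nothing elsewhere relaxes it. If exclusion is not intended, one sentence settles it.

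**Some restriction is unavoidable.** Status measured at 36 weeks or after delivery can only describe women who reach that point. This also stands, and it limits the point to associations that use the enrolment value.

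**Most of the subsample is little affected.** A reader might infer that the nutrient-outcome associations as a whole would be estimated in survivors. The documents do not support that:
- Two of the four draws come after delivery, so an early birth does not prevent them.
- Section VIII.B.5 expects pregnancies to be reported at 3-5 months, so few women in the 1-month group would deliver before their draw.
- The named outcomes are the infant's, and an infant's death does not stop the mother's draw.
- Maternal death removes under 1% of women.

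**Pregnancy losses.** A reader might add the 15% allowance for pregnancies without a live birth to the 10% loss to follow-up and treat the total as missing pairs. Miscarriages and stillbirths lie outside the live-birth denominators of LBW and neonatal mortality, and section VIII.B.7 continues supplement distribution for 12 weeks after them, so a draw may still be possible. Some women lost to follow-up would lack the outcome as well.

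**Assumed rates.** The 12-43% rests on early-birth figures that the protocol does not supply. That is so, and the direction and size of any bias in an association depend on them too.

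**Conclusion.** The point holds in a limited form. As written, the protocol makes assay of the enrolment sample depend on a later draw and provides for no exception. The clear bias is confined to the 36-week group, where births before 36 weeks cannot be paired: 12-43% of that group's LBW cases, about 3-11% over the subsample, under the assumed 3-8% early births of which 60-80% are LBW. General loss to follow-up and maternal death add smaller losses in every group.

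The randomised comparisons of mortality and LBW use the full sample and are not touched. What is at risk is a stated secondary use of the subsample: the associations of nutrient status with LBW and neonatal mortality. The illustration shows that an effect acting only through early delivery would vanish in the paired 36-week women. It does not show that such an effect exists.

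**What to change.** State in sections VIII.B.9 and VIII.B.13 that a woman's two samples are run in the same batch when both exist, and that an enrolment sample without a partner is assayed once its second-draw window has closed. State also that associations of enrolment status with birth outcomes use all available enrolment values, and that pairs are used only for change in status.

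The four draw times can stay randomly assigned. Restricting them to those still attainable at a woman's gestation would itself make the groups differ by gestation at enrolment.

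The cost is a sentence or two in each section. Enrolment draws are already planned for all 20,000 women and the assay groups are sized as if no second draw were missed, so no extra blood collection is needed. The small downside is that unpaired samples run without their partner in the same batch; this does not affect the change analysis, which uses pairs only.
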